### Population

Informed by findings from our development study, students in S3 were chosen because it is an age when experimentation in risk-taking behaviour can start and social norms are established [18]. Consultation with schools and teaching staff also suggested that S3 was an appropriate year due to the young people being more mature and able to understand and engage with different components of PRoGRAM-A (e.g. marketing strategies used by the gambling industry). Finally, from a practical perspective, S3 is the year before students sit their National 4 exams, meaning it would be less disruptive to the school and students.

### Sample

As this is a pilot cRCT (to determine progression to a phase III RCT or not) a power calculation was not required. Six schools across Scotland will take part in the study, four of which will be assigned to the intervention and two of which will be assigned to the control. Four intervention schools balance the need to ensure there is a diversity of schools to inform the delivery of a future phase III RCT but ensure the pilot is small enough to be cost-effective. Depending on the size of the school, the year group size for S3 students could vary between 100 and 150 students. Using a conservative assumption of 85% [16] for attendance on the day of the baseline survey and consent to participate, this gives a projected sample size for the baseline survey of between 510 and 765 students. This range of sample size will enable the proportion of enrolled students completing the baseline questionnaire to be estimated with a 95% confidence interval width ± 2.3% to ± 2.9%, informing planning of the definitive trial.

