### Statistical analysis

Results from the study will be reported using the CONSORT guidelines for pilot and cluster RCTs. The proportion (and exact binomial 95% confidence interval, CI) of students assenting to participate will be estimated, overall and stratified by school. The proportion of students (and exact binomial 95% CI) completing baseline and follow-up questionnaires will be reported overall and by the school. We will summarise the demographic characteristics of students by randomised group and by the school using descriptive statistics.

For each of the quantitative outcome measures on gambling participation, harms, knowledge, and attitudes, the proportion of missing data will be reported overall, by intervention group and by school. Data will be summarised descriptively recording the potential for floor and ceiling effects. We will then pilot the analyses of outcomes that would be performed in a full-scale trial. Outcomes at follow-up will be analysed by multi-level regression modelling, adjusting for baseline values. Estimates for differences between intervention and control (odds ratios and least squares mean differences) will be adjusted for clustering (students nested within schools) and presented alongside 95% CIs. We will also make preliminary estimates of the clustering of outcomes within schools by estimating intra-cluster correlation coefficients (and 95% CIs). As this is a pilot trial, not powered for effectiveness, no hypothesis testing will be performed and no *p*-values presented.

A detailed statistical analysis plan will be prepared, blinded to randomised intervention allocations and accumulating trial data, and finalised prior to database lock.

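### The stated precision for baseline completion (±2.3% to ±2.9%) and the exact binomial intervals planned for the overall proportions make no allowance for clustering in six schools

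*Protocol article*

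**What the plan says.** The protocol article, under Sample, sets the design out as follows: "Six schools across Scotland will take part in the study, four of which will be assigned to the intervention". It adds that "the year group size for S3 students could vary between 100 and 150 students". It then projects baseline numbers: "Using a conservative assumption of 85% [16] for attendance on the day of the baseline survey and consent to participate", which leads to a "projected sample size for the baseline survey of between 510 and 765 students". The precision claim follows. The quantity is "the proportion of enrolled students completing the baseline questionnaire to be estimated with a 95% confidence interval width", and the figure is given with its purpose: "95% confidence interval width ± 2.3% to ± 2.9%, informing planning of the definitive trial". The section mentions neither an ICC nor a design effect.

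Under Statistical analysis, two sentences fix the interval method for the feasibility proportions: "The proportion (and exact binomial 95% confidence interval, CI) of students assenting to participate will be estimated, overall and stratified by school", and "The proportion of students (and exact binomial 95% CI) completing baseline and follow-up questionnaires will be reported overall and by the school". The same section adjusts the between-arm outcome estimates for students nested within schools and plans to estimate ICCs for the outcomes. It extends neither step to the overall assent and completion proportions.

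**The concern.** A binomial interval for a pooled proportion is valid when students respond independently of one another. Here they are sampled in six whole year groups. By the protocol's own account, school teachers describe the study to students (Recruitment), and the survey is ideally held at a special assembly under exam conditions (Assessment and follow-up). Attendance and assent on the day therefore share school-level causes, and some between-school variation is to be expected.

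The stated purpose is to inform a later trial, which would run largely in other schools. For that purpose the effective amount of information depends mainly on six schools and much less on 600 to 900 students. If the interval ignores this, the steering committee and the planners of the definitive trial receive a completion estimate that looks firmer than it is. Completion at baseline and follow-up is also progression criterion 5 in Table 2.

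**Working it through.** **Inputs from the protocol (Sample).** Six schools; m = 100 to 150 students per year group, so n = 600 to 900; p = 0.85; 95% confidence.

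**Input not in the protocol.** The ICC for completion. I assume 0.01, 0.02 and 0.05. At p = 0.85 these correspond to between-school standard deviations, √(ICC × 0.85 × 0.15), of 3.6, 5.0 and 8.0 percentage points.

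**Step 1: reproduce the stated figure.** Half-width = 1.96 × √(p(1−p)/n).
- n = 600: 1.96 × √(0.1275/600) = 2.86%
- n = 900: 1.96 × √(0.1275/900) = 2.33%

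These round to the stated ±2.9% and ±2.3%, so the published range contains no clustering term. The projected survey numbers, 510 and 765, would give 3.10% and 2.53%. The calculation therefore used the full year groups as its denominator.

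**Step 2: add the design effect.** DEFF = 1 + (m − 1) × ICC, and the half-width is multiplied by √DEFF. The z column uses 1.96. The t column uses 2.571 (5 degrees of freedom, six schools), which adds a further factor of 2.571/1.96 = 1.31.

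| ICC (assumed) | m | DEFF | Half-width, z | Ratio to stated | Half-width, t | Ratio to stated |
|---|---|---|---|---|---|---|
| 0.01 | 100 | 1.99 | ±4.0 | 1.41 | ±5.3 | 1.85 |
| 0.01 | 150 | 2.49 | ±3.7 | 1.58 | ±4.8 | 2.07 |
| 0.02 | 100 | 2.98 | ±4.9 | 1.73 | ±6.5 | 2.26 |
| 0.02 | 150 | 3.98 | ±4.7 | 1.99 | ±6.1 | 2.62 |
| 0.05 | 100 | 5.95 | ±7.0 | 2.44 | ±9.1 | 3.20 |
| 0.05 | 150 | 8.45 | ±6.8 | 2.91 | ±8.9 | 3.81 |

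**Step 3: what larger year groups buy.** As m grows with six schools fixed, the z half-width cannot fall below 1.96 × √(p(1−p) × ICC/6). At ICC 0.05 this is 1.96 × √(0.1275 × 0.05/6) = 6.4 points. The binomial formula implies a clear gain from 600 to 900 students (2.9 to 2.3). At ICC 0.05 the gain is only from 7.0 to 6.8.

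**Step 4: coverage of the nominal 95% binomial interval.** Approximately 2Φ(1.96/√DEFF) − 1. For ICC 0.01 and m = 100: 2Φ(1.389) − 1 = 83.5%. For ICC 0.05 and m = 150: 2Φ(0.674) − 1 = 50%.

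**Step 5: near a Table 2 cut-point.** At p = 0.70 the binomial half-width is 3.67 (n = 600) or 2.99 (n = 900). With t on 5 degrees of freedom it runs from 2.99 × 2.07 = ±6.2 (ICC 0.01, m = 150) to 3.67 × 3.20 = ±11.7 (ICC 0.05, m = 100). The amber band, 60% to 69%, is about 10 points wide.

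**The case against.** Several points on the other side have force.

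- **The ICC is assumed.** A reader might infer that the estimate is two to four times less precise than claimed, as a matter of fact. The document does not support that. With z, a two-fold loss needs an ICC of about 0.030 (m = 100) or 0.020 (m = 150), and a four-fold loss needs about 0.15 or 0.10. The larger ratios within my assumed range depend partly on using t with 5 degrees of freedom. This stands, and it is why the size is given as a range.
- **Progression decisions.** A reader might infer that too narrow an interval would push a completion rate into the wrong colour. Table 2 and the Progression criteria section apply no confidence limit, and amber results go to discussion with the steering committee. No category changes mechanically. At the expected 85%, even ±9.1 points leaves the lower limit at about 76%, above the 70% green threshold. The Sample figure also concerns baseline completion only, whereas criterion 5 covers baseline and follow-up. This stands.
- **School variation will be visible.** The proportions are also reported by school, and exact binomial intervals are suitable there. This stands, but it does not correct the overall interval.
- **Six schools only.** As a description of these particular schools, a binomial interval is defensible. The schools are volunteers, possibly chosen purposively, so a school-level interval also rests on an assumption of representativeness. That is fair, but the protocol says the figure is for planning a definitive trial, and the six-schools-only reading does not serve that use.
- **Consistency.** It would be wrong to say that the protocol adjusts for clustering everywhere else. It does so for between-arm outcome estimates only.
- **The denominator.** One might read 510 to 765 against 600 to 900 as an arithmetic error. The quantity is a proportion of enrolled students, so the full year group is a natural denominator. The reference to the sample-size range is loose wording worth about 0.2 points.

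**Conclusion.** The point holds in a conditional form. The range ±2.3% to ±2.9% is an independent-students figure, and the clustered design does not deliver it for the stated planning purpose unless completion hardly varies between schools. The overall exact binomial intervals carry the same assumption into the analysis. For ICCs of 0.01 to 0.05, which are my assumption, and 100 to 150 students per school, the half-width at 85% is about ±3.7 to ±7.0 points (z) or ±4.8 to ±9.1 points (t, 5 degrees of freedom). That is 1.4 to 2.9 or 1.9 to 3.8 times the stated value. With only six schools I would give more weight to the t figures.

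The consequence is false precision in what the steering committee sees and what is used to plan the definitive trial. It does not change a progression category, and it does not affect the number of schools, which the protocol justifies by diversity and cost. It should be corrected, but it is not a reason to hold up the trial.

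**What to change.** 1. **Sample.** Restate the precision with a design effect over a declared ICC range, labelled as an assumption. For example: for ICCs of 0.01 to 0.05, a half-width of about ±4.8 to ±9.1 percentage points at 85% with six schools (t, 5 degrees of freedom), or ±3.7 to ±7.0 with a normal multiplier. Name the denominator (enrolled students, 600 to 900) in the same sentence.
2. **Statistical analysis.** For the overall assent and completion proportions, replace the exact binomial interval with a t interval on the school proportions (5 degrees of freedom with six schools), or with a cluster-robust or beta-binomial interval that has a small-sample correction. Keep the exact binomial intervals within each school.

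The cost is two short text edits and a less favourable stated precision. Design, data collection and progression criteria are unchanged.

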### Recruitment

Schools will be invited to take part in an online information webinar where they can find out more about PRoGRAM-A and what taking part in the pilot RCT would involve. This will help schools make an informed decision about whether they would like to volunteer to take part or not. The school’s webinar invitation will be circulated via existing networks from the research team. This includes dissemination via two voluntary sector organisation (Fast Forward and Larkhall Universal Connections) that have delivered existing gambling prevention work in several schools throughout Scotland. At this pilot stage, there is no restriction on school location, with any state-funded school in Scotland eligible to express interest in taking part.

After the webinar, schools who are interested in finding out more information will email a member of the research team. Depending on the number of schools that express an interest, a purposive sampling frame may be applied to ensure diversity in terms of school size and location. Schools that opt in to PRoGRAM-A will then receive a site visit from a member of the research team where they will be given a more detailed briefing about what is involved and have the opportunity to ask questions. After this site visit, and if they still want to proceed, the school will be registered into the pilot RCT.

Students will be given an information letter about the survey at least 1 week prior to data collection and an oral description of the study from school teachers. Students will have the opportunity to ask questions before deciding whether they want to take part or not. On the day of data collection, students will be invited to give signed assent to participate in data collection. In advance of data collection parents/guardians will be sent an information letter telling them about the research study and giving them an opportunity to opt their child out if they do not want them to participate.

### Randomisation

Schools will be randomised using a remote system set up by Edinburgh Clinical Trials Unit in order to conceal the allocation sequence. The allocation sequence will be stored on a secure server and concealed from all personnel involved in the trial. It will be created, using computer-generated pseudo-random numbers, by a clinical trials unit member of staff with no link to, or contact with, any of the participating schools. The randomisation will be stratified by school size (less than 200/greater than or equal to 200 students on the 3rd year school roll). The PRoGRAM-A intervention to comparator group randomisation ratio within each stratum is 2:1.

Once all schools have been identified, confirmed they wish to take part, and baseline forms have been completed, a designated member of the trial team will contact the Edinburgh Clinical Trials Unit (ECTU) data management team requesting the randomised assignment of all schools. These assignments will then be communicated to the schools by the trial team member. Prior to baseline form completion all trial team members, schools, and students will be blinded; after this point, all will be unblinded.

### Planned intervention

PRoGRAM-A defines gambling as the participation in betting or wagering of things of value (including but not limited to, flat currency, digital currency, and objects of value), which includes all commercial forms of gambling (ranging from lotteries, scratch-cards to online casinos and betting) and gambling-adjacent activities like loot boxes, skin betting, and social casino gambling. It is an adaptation of an effective school-based, peer-led smoking prevention programme, A Stop Smoking in Schools Trial (ASSIST) [14, 15]. As illustrated in our logic model (Fig. 2) the aim of PRoGRAM-A is to identify ‘opinion leaders’ in S3 who are trained to become ‘peer supporters’. Peer supporters are then trained to have informal conversations with anyone in their social networks about the risks of gambling, the influence of gambling marketing, and the links between gaming and gambling [17].

**Fig. 2 Fig2:**
[figure not shown]
PRoGRAM-A logic model

PRoGRAM-A is theoretically grounded in diffusion and network intervention theory. Diffusion theory (also referred to as diffusion of innovation theory), explains how new ideas and social norms are introduced and spread throughout communities [18]. The application of diffusion theory in intervention design relies on identifying influential people who have expertise and credibility among their peers to promote/create new social norms [17]. Social networks are, therefore, a crucial component to support the delivery of diffusion theory. Table 1 summarises the PRoGRAM-A intervention using the ‘Template for Intervention Design and Replication’ (TIDiER) checklist [19].

**Table 1 Tab1:** Description of PRoGRAM-A Intervention using TIDieR checklist

TIDier item	Information on PRoGRAM-A intervention
Brief name	PRoGRAM-A intervention
Why	In the UK, recent evidence has shown that there is a higher prevalence of gambling in young people compared to other addictive behaviours. Early intervention programmes exist for tobacco, alcohol, and drugs, however, similar programmes for gambling are lacking. PRoGRAM-A is theoretically grounded in diffusion and network intervention theory. The application of diffusion theory in the intervention design relies on identifying influential S3 students who have credibility among their peers, who once trained, will have the ability to promote gambling prevention messages and raise awareness of gambling harm in their social network/community
What materials	Peer Supporters will receive 2 days of training, delivered out of school in a community venue. The training is developed from the intervention delivery manual. The catering and venue costs (if any) will be covered by the study. Pin badges and banner pens will be provided for students undergoing the peer supporter training
What Procedures	PRoGRAM-A is a peer-led gambling prevention programme for S3 students. Students will complete a peer nomination questionnaire, nominating those within their year group they respect or look up to. The students with the highest number of nominations will be invited to be peer supporters. At the time of peer nomination, students are not aware that they are identifying influential others in a gambling-related context to prevent biased nomination. Peer supporters undergo 2 days of training covering: (1) what is gambling; (2) gambling and gaming; (3) gambling advertising and marketing; (4) gambling-related harm and keeping safe. They learn how to have informal conversations with anyone in their social network about these topics. These conversations aim to spread new social norms throughout their network and community. After the initial training, the trainers will meet with the peer supporters at three follow-up sessions over the next 8 to 10 weeks to check their progress and to maintain engagement
Who provides	Implementation of the intervention including the 2-day training and the follow-up sessions will be provided by trainers from ‘Evidence to Impact’—a social enterprise that specialises in translating public health into practice. They will be supported by the research team and school staff to arrange suitable times/accommodations for the training and to gather pupils together for the follow-up sessions as well as the interviews and focus groups as part of the process evaluation (all during school hours). Two members of the teaching staff will accompany the peer supporters to the training venue—they will not be involved in the training. They will act as chaperones and will only be called upon if pupil behaviour becomes challenging
How	Each school will identify a main point of contact within the school for the study. The research team will liaise with the school and the trainers to identify and book a suitable training venue as close to the school as possible (ideally walking distance). Transport, if required, will be organised by the research team and trainers with input from the schools. The school will identify staff to accompany the students to the venue and to act as chaperones for the 2 days. The research team will also liaise with the school (and trainers) to book class space and time for the peer supporters to attend the three follow-up sessions and any interviews/focus groups that students are invited to take part in
Where	The initial 2-day training of Peer Supporters will be carried out away from school premises usually in a community venue. Follow-up sessions with Peer Supporters will take place in school during class time. The Process Evaluation interviews/focus groups involving school students will take place in school and during school hours. Interviews with teachers, trainers, and peer supporter’s adult friends/family members can be conducted face-to-face or over the phone/MS Teams at a time/place convenient to the interviewee
When and How Much	Training by ‘Evidence to Impact’ will be carried out over two school days with Peer Supporters. The three follow-up sessions will take place in school during one school period/module 40–50 min each. These will be held at regular intervals over the 8 to 10 weeks after the peer supporter training. Interviews and focus groups will be held after the intervention has been completed and are likely to last between 50 and 60 min depending on how much people have to say
Tailoring	Discussions will take place at each school regarding students with additional support needs and how the intervention can be adapted to make sure all students can be included
How well (planned fidelity assessment)	A process evaluation will provide an assessment for fidelity via: • Recordings of semi-structured interviews and focus groups with peer supporters and other S3 students • Semi-structured interviews with peer supporter’s friends and family members • Semi-structured interviews with teaching staff, intervention trainers, and stakeholders • Observations of two entire delivery cycles of PRoGRAM-A in two separate schools, using semi-structured observation log books

### Comparator

To better understand the influence of peer supporters in the dissemination of gambling prevention and gambling harm messages among youth, we will measure outcomes across six state-funded secondary schools in Scotland randomised to the PRoGRAM-A intervention or to continue with usual practice (recorded before baseline survey completion). The control group school may or may not include the provision of GRH education in school. Although there is no requirement for the provision of gambling prevention education within secondary schools, some have ‘ad hoc’ lessons. If these are present, the information provided will be described in the process evaluation.

### Outcome measures

The primary outcome for this pilot trial is whether progression to a full-scale phase III cRCT of the intervention is warranted. This will be assessed against a set of pre-specified progression criteria (Table 2). Our proposed primary outcome measure for a future phase III cRCT is self-reported gambling participation (measured by asking about types of gambling participation ‘in the last 4 weeks’ and ‘in the last 12 months).

**Table 2 Tab2:** PRoGRAM-A progression criteria

Progression criterion	Red	Amber	Green
1. Successful recruitment of six schools	< 6		6
2. Five schools remain in the pilot study	< 4	4	≥ 5
3. The intervention being delivered with 80% fidelity to the manual	≤ 69%	70–79%	≥ 80%
4. The process evaluation indicates the intervention is acceptable to students and staff	Low	Medium	High
5. 70% of students complete the student questionnaire at baseline and follow-up	≤ 59%	60–69%	≥ 70%

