**Intervention:**

PRoGRAM-A trainers will deliver a 2-day, out-of-school training workshop to Peer supporters. Peer supporters will be nominated by peers among their school year group (S3, age 13–14). Workshops will provide peer supporters with information on four gambling-related topics: (1) what is gambling? (2) gambling and gaming, (3) gambling marketing, (4) identifying harm and reducing risk. Peer supporters will disseminate the information (message diffusion) they have learned among their friends and family over a 10-week period. After the 2-day workshop, PRoGRAM-A trainers will conduct × 3 in-school follow-up sessions with peer supporters to offer support, encouragement, and advice to Peer Supporters as well as monitor and explore the extent of their message diffusion.

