### Pilot cRCT

PRoGRAM-A is an 18-month, two-arm, pilot cluster RCT with an embedded process evaluation which includes a social network analysis and health economic feasibility study, conducted in six schools in Scotland. Following the completion of a baseline student survey assessing gambling attitudes, awareness, and behaviour, four schools will be randomised to receive the intervention (PRoGRAM-A) and two will continue with usual practice. The two comparator schools have been included to test the acceptability of randomisation. Key phases of the study are outlined in Fig. 1.

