#### Assessment and follow-up

Baseline data collection will be conducted before the randomised allocation to PRoGRAM-A or control is revealed to schools. A baseline assessment will be completed in the first term of school with a follow-up survey six months later. Given the logistical challenges of conducting fieldwork in schools, data collection will be paper-based, ideally conducted under exam conditions via a special assembly. Students will be reassured that completing the survey will be completely confidential and anonymous with their name not attached to the survey. Members of the research team and class teachers will be present to help administer the survey, answer any questions students may have, and also support students with additional needs.

Peer supporters will receive three follow-up visits from the trainers. Conducted in school these visits will collect data on the extent of message diffusion among their social network, reinforce key messages, and address any questions or challenges peer supporters may have. Trainers will record any unintended consequence either through observation or direct feedback from school staff and students.

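### At the pilot's six-month survey the 12-month gambling item reaches at least six months back before randomisation, so its piloted odds ratio is attenuated; the 4-week item is not affected

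*Protocol article*

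**What the plan says.** All of this is in the Protocol article.

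- **Outcome measures.** The phase III candidate is "self-reported gambling participation (measured by asking about types of gambling participation ‘in the last 4 weeks’ and ‘in the last 12 months". Both windows sit under one proposed outcome, and the article does not say which leads. The pilot has a different primary outcome: "The primary outcome for this pilot trial is whether progression to a full-scale phase III cRCT of the intervention is warranted".
- **Assessment and follow-up.** "A baseline assessment will be completed in the first term of school with a follow-up survey six months later".
- **Pilot cRCT.** Allocation comes after baseline: "Following the completion of a baseline student survey assessing gambling attitudes, awareness, and behaviour, four schools will be randomised". The Randomisation section agrees.
- **Abstract, Intervention.** After a 2-day training, peer supporters pass on what they learned "among their friends and family over a 10-week period".
- **Statistical analysis.** "We will then pilot the analyses of outcomes that would be performed in a full-scale trial". Follow-up outcomes are modelled with adjustment for baseline values. Odds ratios and intra-cluster correlations are given with 95% confidence intervals, without tests or p-values.

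The article states no follow-up time for phase III.

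**The concern.** A look-back question measures an intervention's effect cleanly only if its window opens after the intervention could act. Here the 12-month window opens about six months before baseline. Gambling in that first half is fixed before any school is allocated, yet it alone settles the follow-up answer as yes.

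At stake is what phase III planners learn. The pilot will report an odds ratio for this item, and in the intervention arm a prevalence, that mix behaviour before and after allocation. Read at face value, they could lead planners to drop a useful outcome, or to size the definitive trial on an effect that the window itself has shrunk.

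**Working it through.** **1. Window overlap (from the protocol's own timings)**

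- Share of the 12-month window before baseline: (12 − 6)/12 = 50%, or 26 of 52 weeks. Randomisation follows baseline, so the share before randomisation is at least this.
- Weeks left after 10 weeks of diffusion: at most 26 − 10 = 16 of 52 (31%), before allowing for the wait for training. Diffusion is itself the intervention, so this is not the only period in which an effect can appear.
- Last 4 weeks: the window opens at about week 22 after baseline, so none of it precedes baseline.

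**2. Size of the attenuation (assumptions, not protocol figures)**

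The only input from the protocol is the 50% 12-month prevalence in 11–16-year-olds cited in the Background. Assumed: gambling occurs at a constant rate, the intervention multiplies that rate by r from baseline onward, and there is no clustering or baseline adjustment.

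With 50% prevalence over one year, the probability of no gambling over t years is 0.5^t. In the intervention arm, post-baseline time counts r-fold. For r = 0.70:

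| Window | Control | Intervention | Odds ratio | Log OR |
|---|---|---|---|---|
| 12 months, asked at 6 months | 50.0% | 1 − 0.5^(0.5 + 0.35) = 44.5% | 0.803 | −0.220 |
| 12 months, wholly after baseline | 50.0% | 1 − 0.5^0.70 = 38.4% | 0.625 | −0.471 |
| Since baseline (6 months) | 29.3% | 1 − 0.5^0.35 = 21.5% | 0.663 | −0.411 |
| Last 4 weeks | 5.2% | 3.7% | 0.694 | −0.365 |

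The overlapping item keeps 0.220/0.471 = 47% of the log odds ratio of a fully post-baseline 12-month window. For r = 0.50 the figure is 0.383/0.881 = 43%, and for r = 0.85 it is 0.107/0.220 = 49%. If students are allowed to differ in their underlying rate (gamma frailty, variance 1 and 3), the range over all runs is 40% to 49%.

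**3. Why no sample-size multiple follows**

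Take prevalence p in each half-year, 50% over the year, and a 20% relative reduction after baseline that falls equally on prior and new gamblers. The true difference is 0.2p, and the 12-month item shows 0.2(50 − p) points.

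| p (assumed) | True | Shown | Squared ratio |
|---|---|---|---|
| 30% | 6 points | 4 points | 2.25 |
| 40% | 8 points | 2 points | 16 |
| 45% | 9 points | 1 point | 81 |

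The squared ratio roughly approximates the sample-size multiple. It runs from about 2 to 81 over plausible values of one number that the protocol does not give.

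**4. Baseline adjustment**

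A baseline yes on the 12-month item does not show whether the student gambled in the six months just before baseline, which forces a yes at follow-up, or only in the six months before that, which does not. Adjustment may recover precision, but it cannot sort these students. A baseline no is informative: a truthful yes at six months then means gambling since baseline.

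**The case against.** **Two trials are being read as one.** The outcome is proposed for phase III, while the six-month interval belongs to the pilot. A reader might infer that the phase III primary outcome will be measured at six months. The article does not say so, and with 12 months or more of follow-up the overlap disappears. This stands, and it confines the point to the pilot's estimates and their use.

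**The same sentence contains a clean window.** A reader might infer that the whole candidate outcome is diluted. It is not: the 4-week item lies wholly after randomisation. This stands.

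**Nothing in the pilot turns on the item.** None of the five criteria in Table 2 uses gambling participation, and no hypothesis is tested. Piloting two windows is a normal way to choose between them. This stands, and it keeps the point at the level of an inexpensive improvement. It does not remove the need to tell planners that one of the two estimates is attenuated by construction.

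**The item still registers an effect.** A reader might conclude that it cannot. Every scenario above shows some difference, and among baseline non-gamblers the item picks up new gambling, which is what the intervention aims to delay or prevent. If the effect fell only on students who had not gambled before baseline, the 12-month item would show the whole difference in points. This stands.

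**Joint listing can be settled elsewhere.** How the two windows combine may be left to the statistical analysis plan, which is not shown. That is accepted; the overlap itself comes from the timings fixed in the article.

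**Conclusion.** The point holds for the 12-month item at the pilot's six-month survey. At least half its window precedes randomisation. This is arithmetic on stated timings and needs no assumption. Its piloted log odds ratio is then roughly halved under constant-rate gambling (43% to 49% of the undiluted value, or 40% to 49% once students may differ in their rates). These sizes assume 50% annual prevalence, an effect from baseline onward, and no baseline adjustment. The true size depends on half-year prevalences absent from the protocol.

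Three stronger readings are not supported: that any effect on the proposed outcome is diluted, that phase III is compromised, and that a particular multiple of the sample size is needed. The first ignores the 4-week window, the second assumes a phase III follow-up time that is not stated, and the third rests on an assumed prevalence. The pilot's progression decision is untouched.

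**What to change.** - Name one candidate primary outcome at six months: the existing 4-week item, or an added item asking about gambling since the last survey.
- Keep the 12-month item as a baseline covariate or descriptor, or tie it to a follow-up of at least 12 months.
- State that the six-month effect estimate on the 12-month item will not be a planning input for phase III.

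The Abstract describes the follow-up surveys in the past tense. If those data are already collected, the questionnaire cannot change. In that case, designate the 4-week item in the analysis and report, and state the overlap beside every 12-month estimate.

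**Cost.** One added or reworded item, or one or two sentences. A reworded follow-up item would no longer match its own baseline item, which the model uses for adjustment, nor the 12-month wording of the national survey cited in the Background. Adding an item avoids losing either match. The 4-week item is free of overlap but less common (5.2% against 29.3% since baseline in the constant-rate example), so planners should weigh its lower prevalence when choosing between the two.
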